### Qualitative data analysis

Data analysis for the rapid ethnographic assessments will be done manually using the framework analysis approach [56]. Manual analysis enables the three site teams to manage a range of data which consists of notes from observations, sketch maps, interview, and discussion group transcripts. Themes will be shared and discussed across the sites to arrive at a shared coding framework. Following the identification of themes, indexing (coding) and charting (cutting and pasting data according to thematic areas) will be done simultaneously at each site. Mapping (visual display of data) allows researchers to identify patterns, associations, and concepts, allowing descriptive and analytical memos to then be produced from these charts.

We will produce a short report to provide an overview for the wider study team on each community, and we will also aim to write a short feedback flyer to share with the communities based on the same short report. Once an initial report has been completed and summary findings shared with the participating communities, we will conduct a finer analysis of the data from the rapid ethnographic assessment, using a thematic content analysis—the approach we will also use for the qualitative data collected during the trial from interviews and group discussions.

For the qualitative data collected during the conduct of the trial from the IDIs and group discussions, we will again develop a shared coding framework, drawing from both the topic guides, learning from the rapid ethnographic assessments and new themes, which may come from the data collected. Analysis will be conducted by the site-specific research teams, and regular (electronic) meetings across the Ugandan and South African teams will support data interpretation. This will provide a more comprehensive understanding of men’s mobility and PrEP use across the trial groups and in the different settings/countries, as well as the acceptability and feasibility of the intervention. Where required to support the analysis, data sharing between sites will only involve the sharing of anonymised data through a secure data enclave.

### Health economics analysis

#### Cost analysis

We will analyse the incremental financial and economic costs of implementing either intervention over routine care for these populations from the perspective of the provider, the South African or Ugandan government. Standard of care approaches to retaining people in care will be identified from routine government services for HIV in each recruiting country. Total and average cost per person retained at 3 and 6 months will be estimated from the perspective of the provider and the public healthcare system in each country. Additionally, we will estimate PrEP coverage during periods of sexual activity. We will calculate annualised capital and recurrent costs at facility and any other relevant implementation level. Non-annualized annual economic costs will be used to inform the budget impact for each country and inform governments and other relevant funders of the intervention’s affordability.

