Men who are mobile due to work or looking for work are a key population at high risk of acquiring HIV [21]. High HIV prevalence remains disproportionately high in this population in sub-Saharan Africa. Estimates range from 0.95% to 54% among truck drivers [24], 39.5% to 42% among farm workers [25], 26% among unemployed men in South Africa [26], and 40% among men in fishing communities in Uganda [27]. As Africa’s large youth bulge moves into young adulthood, the search for work and associated mobility will further increase. Despite this, PrEP intervention studies have not included these populations [28], and, as such, a real-world delivery model for HIV prevention in mobile men has not been developed. One specific concern is that those who are mobile for work may require more flexible PrEP delivery systems to allow for extended periods away from home [4].

Political decisions regarding rollout and delivery models need to take into account implementation needs and cost-effectiveness. Recent economic analyses comparing CAB-LA to oral PrEP have shown mixed results. Seven studies modelled data and scenarios specific to South Africa [29–35], but with the exception of two [35, 36], none was based on trial or implementation study data. Additionally, one study assessed costs for men who have sex with men and transgender women in the USA [37]. Economic analyses comparing CAB-LA to oral PrEP based on data from implementation and countries other than South Africa are therefore needed. The Mobile Men study will provide data on the cost and outcomes of ED PrEP and HIV antibody test monitoring of CAB-LA to be used for such economic analyses. We also, for the first time, will provide cost data for Uganda for oral PrEP and CAB-LA PrEP. For this, we will use the HIV Synthesis model, an individual-based model that includes both oral and long-acting injectable PrEP, while accounting for drug resistance [36, 38]. This is particularly important for CAB-LA, given its tail dosing and the potential for cross-resistance between cabotegravir and dolutegravir, the cornerstone drug of first-line HIV treatment globally.

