## Objectives {7}

The overall objective of the Mobile Men study is to assess the effectiveness and implementation of CAB-LA and oral TDF/FTC (both daily and ED) amongst men who are mobile for work in South Africa and Uganda, through comparison of uptake, retention in care, coital coverage, and participant choice.

The primary user effectiveness objective is to compare short-term (9 months) and longer-term (18 months) PrEP persistence patterns across different PrEP modalities (oral and injectable) amongst men who are mobile for work in South Africa and Uganda.

The primary implementation objective is to compare adoption (uptake and choice) across the different PrEP modalities (oral and injectable) amongst men who are mobile for work in South Africa and Uganda.

The secondary clinical objectives are as follows:To compare the effective coital coverage of oral daily/ED TDF/FTC versus CAB-LATo describe the safety, tolerability, and acceptance of all methods, as determined by self-reported side effects, adverse events (AEs), and reasons for PrEP pause or discontinuation

The secondary implementation objectives are as follows:To understand the reach of PrEP for mobile men and understand the barriers to, and facilitators of, uptake amongst those at risk who do and do not accept oral or injectable PrEPTo describe adoptionTo identify characteristics of men who adopt oral PrEP versus CAB-LATo describe patterns of use of daily, ED, and long-acting PrEP amongst different groups of mobile menTo understand the Implementation of ED and long-acting PrEP for mobile men amongst service providers to inform scale-upTo understand the feasibility and fidelity of delivering ED and long-acting PrEP in different settingsTo describe how ED and long-acting PrEP are delivered in practiceTo describe the service-level needs to implement ED and long-acting PrEPTo evaluate acceptability and implementation of antibody-based HIV status monitoring for CAB-LATo assess the total and average cost of oral PrEP and CAB-LA in South Africa and Uganda under study conditions from the provider perspective (maintenance)

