### Outcomes {12}

The trial will have two co-primary outcomes:

User effectiveness co-primary outcome: This will assess persistent use of PrEP during the randomised period and throughout the full follow-up period. Persistent use of PrEP during the randomised period will be defined as a binary outcome. Participants randomised to the CAB-LA arm who receive all injections as per schedule (initial injection at month 0, followed by injections at months 1, 3, 5, and 7, with an acceptable window of ±7 days for each injection) will be considered “persistent on PrEP”. Participants who do not receive all injections as scheduled will be classified as “non-persistent on PrEP”, regardless of the frequency or timing of self-reported condomless sex. Participants randomised to the oral PrEP arm will be considered “persistent on PrEP” if they attend scheduled 3-monthly visits, receive sufficient PrEP to maintain supply until the next visit, and have detectable TFV-DP levels in DBS.During the full follow-up period (18 months), persistence will be assessed as a multinomial outcome with the following categories: single modality, consistent use; multiple modalities, consistent use; single or multiple modalities, inconsistent use; and never started PrEP.Implementation co-primary outcome: This will compare the adoption (uptake when offered and choice preference of the different modalities). Uptake is defined as the proportion of participants who are offered and subsequently take PrEP (oral PrEP arm versus CAB-LA arm) during the 9-month randomised period. Choice preference will be measured as the proportion of participants who choose and use each modality (daily or ED oral PrEP or CAB-LA), captured at the start and the end of the subsequent 9-month choice period.

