Secondary outcomes include the following:Short-term flexible PrEP persistence: A binary outcome that is analogous to the user effectiveness co-primary outcome but with more flexibility allowed on visit windows, specifically an acceptable window of −7 to + 28 days for scheduled injections at months 3, 5, and 7 in the CAB-LA arm and for scheduled visits at months 4 and 7 in the oral PrEP arm.Effective peri-coital coverage of PrEP: A binary outcome measuring whether, at the time of last condomless sex, the participant was “covered” by PrEPSafety, tolerability, and acceptance: Assessed based on self-reported AEs and the reasons for PrEP pause or discontinuationReach: Evaluated qualitatively through three serial rapid ethnographic assessments capturing information on awareness and reach of PrEP amongst mobile menAdoption: This will be evaluated by (i) comparing the characteristics of men who uptake oral PrEP with those who uptake CAB-LA when offered at month 0, (ii) comparing the characteristics of men who choose oral PrEP with those who uptake CAB-LA when given the choice at month 9, and (iii) describing patterns of use of daily, ED, and long-acting PrEP during months 9–18 of the trial and the transitions between these modalities.Implementation: Evaluated using qualitative data collected from service providers, with a focus on fidelity and feasibilityMaintenance: Evaluated through calculation of total and average cost of oral PrEP and CAB-LA in South Africa and Uganda under study conditions, from the provider perspective

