**Intervention**											
CAB-LA injection			X	X	X		X	X			
Oral PrEP dispensed			X	X		X		X			
**Assessments**^**2**^											
Locator information	X			X		X			X	X	
Demographics	X										
Risk and mobility (short CRF)	X			X	X	X	X	X	X	X	
Risk and mobility (Long CRF)	X								X		X
PrEP adherence				X	X	X	X	X	X	X	X
Adverse events			X	X	X	X	X	X	X	X	X
IDIs				X		X	X		X	X	X
FGDs				X					X		X
Surveys	X								X		X
HIV test	X			X	X	X	X	X	X	X	X
STI screen	X								X		
DBS	X			X	X	X	X	X	X	X	X
Blood pressure	X				X	X			X	X	X
BMI	X				X	X			X	X	X
CrCl if ≥ 30 years	X										
HepBsAg	X										

^1^Visit schedule for choice phase is dependent on choice of PrEP made at month 9 and at each subsequent visit. ^2^Done at visits corresponding to the intervention received by the participant; *CAB-LA*, long-acting injectable cabotegravir; *PrEP*, preexposoure prophylaxis; *CRF*, case report form; *IDIs*, Iin-depth interviews; *FGDs*, focus-group discussions; *HIV*, human immunodeficiency virus; *STI*, sexually transmitted infection; *DBS*, dried blood spot; *BMI*, body mass index; *CrCl*, creatinine clearance; *HepBsAg*, hepatitis B surface antigen

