### Cost-effectiveness analysis

We will combine results regarding the incremental cost from above and HIV synthesis model outputs regarding the incremental number of infections averted, life-years saved, and disability-adjusted life-years (DALYs) averted by each strategy (oral or injectable PrEP) over baseline (no scale-up of PrEP) to calculate the incremental cost-effectiveness of each intervention, as well as the strategy of offering either intervention. The HIV synthesis model will be fitted to epidemiological data to represent the current HIV epidemics in South Africa and Uganda and be parameterised and structured to account for important behavioural heterogeneity, including how behaviours and PrEP choices vary among cohort participants and within persons over time. The synthesis model will be used to calculate costs over the long term, as well as life-years lost and DALYs, with costs and effectiveness calculated over a sufficiently long period to represent the difference in the main impacts between strategies but at least over 20 years.

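### Cost per person retained is fixed at months 3 and 6, which are not visits common to both arms, and the stated cost-effectiveness ratios do not rank oral, injectable and choice

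*Protocol article*

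**What the plan says.** All references are to the protocol article.

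- **Cost analysis.** One output is given fixed time points: "Total and average cost per person retained at 3 and 6 months will be estimated". The section does not define retained at those months. It takes the costs of either intervention as increments over routine care.
- **Visits, CAB-LA arm (Outcomes {12}).** "initial injection at month 0, followed by injections at months 1, 3, 5, and 7, with an acceptable window of ±7 days for each injection".
- **Visits, oral arm (Outcomes {12} and Table 1).** The flexible-persistence outcome applies its wider window "for scheduled visits at months 4 and 7 in the oral PrEP arm". Table 1 shows oral PrEP dispensed at months 0, 1, 4 and 7. A footnote to its assessments reads "Done at visits corresponding to the intervention received by the participant", so a column in the table need not apply to both arms. Table 1 has no month-6 column.
- **Horizons (Objectives {7}).** The primary user effectiveness objective is to "compare short-term (9 months) and longer-term (18 months) PrEP persistence patterns across different PrEP modalities".
- **Cost-effectiveness analysis.** Incremental costs from the cost analysis are combined with modelled health effects gained "by each strategy (oral or injectable PrEP) over baseline (no scale-up of PrEP) to calculate the incremental cost-effectiveness of each intervention". The strategy of offering either product is evaluated as well. No direct CAB-LA-versus-oral ratio is named.
- **Background and rationale {6a}.** "Economic analyses comparing CAB-LA to oral PrEP based on data from implementation" are described as needed, and the study is to supply data for them. The end of the same section says that the evidence should help governments and donors set priorities for prevention spending.

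**The concern.** A cost per person retained is a ratio, and both parts depend on the date at which it is cut. If one arm has a visit at that date and the other does not, the count of men retained and the accumulated delivery cost rest on different conventions in the two arms. Months 3 and 6 also come before the trial's own horizons and before the choice phase, so this output says nothing about choice, although choice is one of the modelled strategies.

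The second matter is ranking. Oral, injectable and choice are competing policies for the same men. A ratio of each against no scale-up can look acceptable for CAB-LA even where its added benefit over oral is bought at a much higher price. A reader setting priorities needs the second quantity, and the text does not name it.

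**Working it through.** The plan gives no cost, effect or threshold figure on this point, so there is none to reproduce. The first three steps use the visit schedule. The last two use algebra with assumed values.

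**1. Common visits.** From Outcomes {12} and Table 1:
- CAB-LA: {0, 1, 3, 5, 7, 9}
- Oral: {0, 1, 4, 7, 9}
- Common to both: {0, 1, 7, 9}

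| Month | CAB-LA visit | Oral visit | Nearest CAB-LA visits | Nearest oral visits |
|---|---|---|---|---|
| 3 | yes | no | 3 | 1 and 4 |
| 6 | no | no | 5 and 7 | 4 and 7 |
| 9 | yes | yes | 9 | 9 |

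**2. Effect on the count retained.** The retention section {18b} dates loss to follow-up from the last study visit. Suppose that rule were used here. A man who leaves for good between months 3 and 4, having attended every visit due, has a last visit at month 3 if on CAB-LA and at month 1 if on oral. He could count as retained at month 3 in one arm and not in the other. At month 6 the next visit is month 7 in both arms, so the same rule treats the arms alike, but what it measures is attendance at month 7.

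**3. Effect on cost.** Scheduled product-delivery contacts, CAB-LA to oral:
- through month 3, counting the month-3 injection: {0, 1, 3} against {0, 1} = 3:2 = 1.5
- through month 3, not counting it: 2:2 = 1.0
- through month 6: {0, 1, 3, 5} against {0, 1, 4} = 4:3 = 1.33
- over the randomised phase: {0, 1, 3, 5, 7} against {0, 1, 4, 7} = 5:4 = 1.25

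The month-3 figure thus moves between 1.0 and 1.5 on a convention that is not stated.

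**4. Ratios against a baseline.** Write A for oral, B for CAB-LA and 0 for the baseline.
- Against baseline: R_A = (C_A − C_0)/(E_A − E_0), and R_B likewise.
- Head to head: R_BA = (C_B − C_A)/(E_B − E_A).
- Since (C_B − C_0) − (C_A − C_0) = C_B − C_A, and the same holds for effects, the baseline cancels. R_BA can be recovered from the increments when the baseline is the same for both strategies.

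Two illustrations, with all values assumed:
- Oral adds cost 100 and averts 10 DALYs; CAB-LA adds 300 and averts 15. R_A = 100/10 = 10, R_B = 300/15 = 20, R_BA = (300 − 100)/(15 − 10) = 40.
- Total costs are 100 (baseline), 150 (oral) and 240 (CAB-LA), with effects over baseline of 10 and 16. R_A = 50/10 = 5.0, R_B = 140/16 = 8.75, R_BA = (140 − 50)/(16 − 10) = 15.0.

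For the range, let f be oral's health gain as a share of CAB-LA's, with 0 ≤ f < 1. Then R_B = f·R_A + (1 − f)·R_BA, so R_BA = (R_B − f·R_A)/(1 − f). With R_A = 10 and R_B = 20:
- f = 0 gives 20
- f = 1/2 gives (20 − 5)/0.5 = 30
- f = 2/3 gives 40, as above
- f = 0.9 gives (20 − 9)/0.1 = 110

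So when CAB-LA has the larger health gain and the higher ratio against baseline, its head-to-head ratio is at least as high as its baseline ratio and has no upper limit. The two baseline ratios alone do not determine it; f is needed too.

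**5. The two baselines.** If routine care and no scale-up differ, a stated ratio becomes (C_B − C_routine)/(E_B − E_0), and its numerator is off by C_0 − C_routine. The head-to-head contrast is unaffected as long as each baseline is the same for every strategy.

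**The case against.** The strongest reply has four parts.

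- **Scope.** Only cost per person retained is tied to months 3 and 6. Annualised costs, budget impact and model outputs over at least 20 years are not. This stands. A reader might infer that the health-economic results as a whole hang on these months; the documents do not support that.
- **Retention needs no visit on the exact date.** Later attendance can establish it, and resource use from the case report forms can be accumulated to any day. This also stands, most clearly for month 6, where month 7 is the next visit in both arms. The problem is comparability and definition; retention at these months is not unobservable.
- **The comparator does not block a head-to-head answer.** A shared baseline cancels, and the cost-effectiveness section sets its horizon so as to show differences between strategies. The stated cost objective is total and average cost per modality, and the background promises data for comparative analyses. A reader might infer that the plan cannot yield CAB-LA versus oral, or breaks a promise of such a ratio. Neither follows.
- **An article condenses.** Detail may sit in the full protocol or a health-economics plan. That would excuse an unstated definition of retained. It does not excuse two stated choices: months that misfit the printed schedule, and ratios for competing options that are set out only against baseline.

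The numerical illustrations rest on assumed values and show a general property of such ratios. They do not estimate an effect in this trial.

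**Conclusion.** The point holds in limited form and should be acted on. Neither of the two stated time points is a visit common to both arms, and neither matches the 9- or 18-month horizon. The consequence for cost per person retained is clearest at month 3, where relative delivery contacts range from 1.0 to 1.5 by convention. The stated cost-effectiveness ratios allow CAB-LA versus oral to be derived, but do not themselves rank oral, injectable and choice. How far a head-to-head ratio would exceed the baseline ratios here cannot be known from the documents, which give no costs, effects or threshold. The differing baselines for costs and effects may be one and the same in practice, but the text does not say so.

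This rests on reading Table 1 with its footnote as giving each arm its own visits, and on month 9 being attended by both arms at entry to the choice phase. Cost is a secondary outcome, and no inference on the effectiveness outcomes is affected.

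**What to change.** 1. Replace months 3 and 6 by month 9, a visit common to both arms, and month 18. Use one retention definition, with one window, applied identically to both arms.
2. Do not use the co-primary persistence definitions as the main denominator. They differ by arm: every injection within ±7 days for CAB-LA; attendance, supply and detectable drug for oral. Cost per person persistent by those definitions can be an additional result.
3. Describe the month-18 figure as covering the randomised phase plus the choice phase, and not as a CAB-LA-versus-oral contrast.
4. State one common baseline for costs and effects, or say explicitly that routine care and no scale-up are the same scenario.
5. Keep the ratios against no scale-up. Add a full incremental analysis that orders no scale-up, oral, injectable and choice by cost, removes dominated options, reports each remaining option against the next less costly one, and gives CAB-LA versus oral explicitly.

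The cost is small: wording in the health-economics plan and recombination of outputs already planned, with no new data or visits. Trial status puts the end of follow-up at April 2026; the wording should be settled before costs are analysed.

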#### Health economics

Cost data will be collected using bottom-up and top-down costing, drawing on expenditure reports, resource use from CRFs, from the provider perspective. We will combine these with relevant, up-to-date information on public sector prices and salaries in either country. At the mid-point of implementation, data collectors will conduct a time-and-motion study with study staff involved in implementation at each site to estimate staff time and resources used on key activities. Trial resource use will be adapted to represent potential rollout in routine care.

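### Budget impact is assigned to economic rather than financial costs, so the affordability figure can overstate, by an amount the article does not allow to be derived, the new money a government would need

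*Protocol article*

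**What the plan says.** Under Health economics analysis, the Cost analysis section commits to two cost sets, the "incremental financial and economic costs of implementing either intervention over routine care", taken "from the perspective of the provider, the South African or Ugandan government". On capital it states: "We will calculate annualised capital and recurrent costs at facility and any other relevant implementation level". The next sentence turns to affordability: "Non-annualized annual economic costs will be used to inform the budget impact for each country". It adds that the result will "inform governments and other relevant funders of the" affordability of the intervention.

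The data-collection section headed Health economics says that costs will be combined with "relevant, up-to-date information on public sector prices and salaries in either country", that a time-and-motion study of study staff will be done, and that resource use seen in the trial will be adapted to reflect rollout in routine care.

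The article does not define financial or economic cost. It gives no explicit use for the financial set.

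**The concern.** A budget impact and an economic cost answer different questions. The first asks what extra expenditure the payer must find, year by year. The second values everything used up, whether or not new money changes hands. A nurse already on the payroll, a room already in use or a vehicle already owned has an opportunity cost but may add nothing to next year's budget.

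The pairing with non-annualised costs is a second difficulty. An economic costing normally spreads a capital item over its useful life, as the preceding sentence of the article does. Charging the whole item in one year makes sense when the item is bought in that year, which is the cash-flow view. Attached to economic costs, it could place the full value of an already owned asset in a single year. The wording may simply be a slip for financial costs, but the article does not show that.

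At stake is the figure that governments and funders would use to judge affordability. Table 2 names affordability under the Maintenance domain, and informing government decisions on injectable PrEP is a stated purpose of the trial.

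**Working it through.** The article states no cost or budget figure, so there is nothing to reproduce. What can be checked is the direction of any error and what it depends on.

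**Definitions (for this check; the article gives none)**
- F: new cash outlay under trial conditions.
- X: existing resources redeployed to PrEP, valued at opportunity cost, with no new cash in the trial.
- D: items supplied to the trial without payment, valued at a price. The Trial Management Group section names a manufacturer as product provider, but the terms of supply are not stated.
- a, b: the shares of X and D, each from 0 to 1, that become real payments at rollout.

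**Formulas**
- Economic cost: E = F + X + D.
- Financial cost under trial conditions: F.
- Government cash need at rollout: C = F + aX + bD.
- Gap: E − C = (1 − a)X + (1 − b)D, which cannot be negative.

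**Illustrations with assumed values, F = 100**

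| X | D | a | b | E | C | E relative to C |
|---|---|---|---|---|---|---|
| 40 | 0 | 0 | – | 140 | 100 | 40/100 = 40% too high |
| 40 | 60 | 0 | 1 | 200 | 160 | 40/160 = 25% too high |
| 40 | 60 | 1 | 1 | 200 | 200 | 0% |

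In the last row the trial-condition financial cost is 100 against a need of 200, which is 50% too low.

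**General range.** If q is the share of E that needs no new payment at rollout, the overstatement is 1/(1 − q) − 1. For q = 0, 0.1, 0.2, 0.3 and 0.5 this is 0%, 11%, 25%, 43% and 100%. The documents give no value of q, and q = 0 is compatible with them.

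**Non-annualised capital.** Take an assumed item with a 5-year life at 3%. The annual economic charge is 0.03/(1 − 1.03^−5) = 0.218 of its value. Charging the full value in one year is 1/0.218 = 4.6 times as much. If government already owns the item, this adds cost where there is no new outlay. If government must buy it for rollout, the full charge in the year of purchase is what a budget should show. The same rule is therefore right for expenditure and wrong for an owned asset, which is why the cost concept it is attached to matters.

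**The case against.** The strongest reply is that nothing in the article shows the figure will be too high. Costs are incremental over routine care, use public-sector prices and salaries, and start from resource use adapted to rollout. Delivery in the trial is by research institutes, with mobile clinics in South Africa, and the KwaZulu-Natal recruitment section describes public clinics as short of resources. If government would have to hire the staff, buy the clinics and pay for the product, economic cost equals cash need. Moving to financial costs as incurred in the trial could then err the other way, because supplied product might be left out. Valuation rules for shared staff and equipment also normally sit in a fuller costing plan.

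Most of this stands. It removes any certainty about the direction and size of error, and it means the remedy cannot simply be trial-condition financial costs. It does not remove the mismatch: the article plans both cost sets and names one for the budget. That is a stated choice, not a detail left to another document.

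A reader might also infer that the ranking of the products on budget impact would shift. The Background says long-acting PrEP brings more clinic visits and needs trained staff, and Table 1 shows five injection visits against four oral dispensing visits in the randomised phase. The documents do not say how much existing staff time each product would use, or how it would be valued, so they do not support a claim about ranking.

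**Conclusion.** The point holds as a mismatch between the cost concept and its purpose. Budget impact and affordability should rest on expected government expenditure; the article rests them on economic costs, and attaches to those a treatment of capital that belongs to expenditure. The affordability figure can overstate the new money needed, from zero upward under the definitions above. Whether it exceeds zero depends on how much existing resource is counted and how much of it would need new payment at rollout, neither of which the documents give. The percentages in the working are illustrations under assumed inputs, not estimates for this trial.

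A reader might go further and conclude that the figure is certainly too high. Incremental costing, public-sector prices and the planned adaptation to rollout leave room for no overstatement at all.

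The consequence is confined to a secondary health-economics output. Budget impact is not itself among the listed objectives or outcomes, which name total and average cost. The co-primary analyses and the sample size are untouched.

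**What to change.** Replace the budget-impact sentence in the Cost analysis section with:

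> Non-annualised annual financial costs (projected government expenditure at rollout, with trial-supplied CAB-LA and TDF/FTC valued at public-sector prices and any additional staff or capital needed included) will be used for the budget impact; annualised economic costs will be used for average cost and cost-effectiveness.

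The words in brackets are essential. Without them, financial cost could be read as spending under trial conditions, which could understate the need.

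The cost is small: both cost sets, public-sector prices and adaptation to rollout are already planned. The downside is that for each shared resource the analysts must judge whether rollout needs extra capacity, and those judgements should be recorded.
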